#### Synopsis of program content

This ranges from group activities focusing on executive skills (concentration, attention, planning), cognitive-emotional regulation (use of Mindfulness, managing rumination and mood swings), through to reducing health risk behaviors (nicotine and alcohol consumption) and enhancing health-promoting behaviors (periods of moderate-intensity to high-intensity exercise).

#### Extended session (2.5 hours)

When participants arrive, they are welcomed and given a quick overview of the session program (see Table 2). The “topic of the day” (e.g. mood regulation, problem solving, etc.) is briefly outlined and any experiential tasks are explained, written or other resources are distributed and the structured intervention begins (e.g. tennis (Physical Well-being Module) or Anxious Art (Social Participation Module). Next, there is a 25–30 minute break when participants listen to a “tea-cup talk.” This is a brief, informal lecture on a specific topic followed by an interactive discussion, summarizing and feedback. Useful webpages and phone “apps” are also identified. At the completion of the talk, participants return to the structured intervention activity for about 1 hour. To signal the close of the session, “housekeeping issues” (dates of specific activities, equipment needed, etc.) are addressed. Participants are thanked for attending and encouraged to attend the next session.

**Table 2 Tab2:** Format of extended group session (2.5 hours)

Activity	Duration
Welcome and overview	5 minutes
Introduction of topic	5 minutes
Group activity	60 minutes
Module A- example: Anxious Art	
Module B- example: tennis	
Re-introduce topic, distribute hand-outs	5 minutes
Activity component	5–10 minutes
Skills component	5–10 minutes
Summary and feedback	5 minutes
Return to group activity (Continue module A or module B activity)	50 minutes
Reminders and close of group	5–10 minutes

#### Short session (1.5 hours)

When participants arrive, they are welcomed and given an overview of what the session will include. Any housekeeping issues (dates, equipment use, etc.) are addressed. A short talk is given on a specific topic (5–10 minutes) and hand-outs are distributed. This is followed by a 1-hour activity such as cardio boxing (module B: Physical Well-being) or e-Health Lounge (module A: Social Participation). The session concludes with a reminder about the session topic of discussion. Participants are then thanked and encouraged to attend the following week.

### Sample size/Power calculation

This feasibility study will allow us to undertake sample size calculations for future multi-center studies and inform the selection of outcome measures. There are no studies that have undertaken group interventions that target the same variables and outcomes specifically as this study and, most importantly, as both modules are deemed “active” interventions, we do not anticipate large between group differences associated with the modules. However, based on previous data from published clinical observational studies and controlled trials (that have estimated means scores on the SOFAS and FAST to be about 60–70 and 20–25 at baseline and clinically significant improvement to be associated with score changes of about 15–25 % over about 10–20 weeks), we have made a conservative estimate that each module can produce a statistically significant improvement in the scores (*p* < 0.05 with > 80 % power) on the 2 most important primary assessments: namely, the continuous measures of functioning (the FAST and SOFAS) of > 5 points between week 1 and week 9, and between week 11 and week 19 (we have not made any predictions associated to the 12-month follow-up).

Randomization of 120 individuals, with predicted retention of about 90–100 individuals at week 8 will give a sample size that is sufficient to detect clinically significant changes in functioning with medium to large effect sizes. Also, we predict this initial recruitment level would provide follow-up assessments on about 72–80 individuals at week 19 and about 66–70 individuals at 12 months.

Information on categorical outcomes (such as vocational status) is likely to be available on a larger sample, as it does not require the individual to participant in self-rated or observer-rated assessments, nor attendance for laboratory tests. Feedback is encouraged by all participants and is included as part of the week-to-week “summary/discussion” at the end of each group session. As such, whilst this information will be used for planning modifications to the programme, it is not being formally collated and analyzed.

### Statistical analysis plan

All data are entered into and analyzed descriptively using SPSS, version 21 (SPSS Inc., Chicago, IL, USA). As this research was conducted in health service settings (with participants, clinicians and/or administration information being utilized\, there are variable rates of missing data, which will be taken into account in the analysis plan.

Primary analyses will be based on the intention-to-treat (ITT) sample: i.e. everyone who was randomized will be included in the analysis regardless of participation (full or partial or none) in the intervention groups. The primary outcome is the change in FAST (self-rated) and SOFAS (observer-rated) score pre-intervention to post intervention (e.g. between weeks 1–8 and then weeks 11–19). A preliminary analysis will be reported on week-8 outcomes once the target sample has completed this stage.

Further analyses will evaluate the scores at the end of the follow-up period and changes in secondary outcome measures. Categorical outcomes, such as vocational status will be examined using simple (chi-squared) and logistic regression models.

Mixed-model repeated measures analyses may be used for some analyses because of the ability of this approach to include participants with missing data without using discredited techniques such as last observation carried forward.

Additional analyses will include per-protocol analyses and statistical methods to explore factors that moderate outcomes, including attrition rates and, if appropriate, levels of presenting severity associated with significant social, clinical or functional improvement or change in vocational status.

Finally, some basic analyses will be undertaken of anthropometric and metabolic screening data. The latter will include a review of the uptake of these screening tests by study participants, and any barriers to this approach, as well as analysis of the findings. This pilot data will be used to inform power calculations for future studies.

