## Methods

### Design

This is an un-blinded, two-arm, parallel group RCT with a cross-over design. The duration of the controlled phase of the RCT is 19 weeks. Participants will complete a pre-randomization assessment and after randomization to commence with module A or module B, they will complete further assessments at week1 and week8 (beginning and end of first module) and week11 and week19 (beginning and end of second module). The post-trial follow-up assessment will be undertaken 12 months after randomization.

The design will allow us to answer questions about the benefits of each module (comparison across groups between weeks 1–8; then comparison across weeks 11–19), and also whether benefits from or engagement with either module can be predicted by week 1 measures (e.g. are men more likely to engage with the module that targets activity whether this is offered for weeks 1–8 or for weeks 11–19? Do more individuals drop out in weeks 11–19 compared to weeks 1–8, no matter which module is being provided?).

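### Attrition is named beside presenting severity as a moderator of outcome; because it follows randomisation and can result from poor response, an exploratory stayer-leaver comparison is liable to mislead

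*Protocol article*

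**What the plan says.** The sentence at issue is in the Statistical analysis plan section and concerns secondary, exploratory work. Beside per-protocol analyses it plans "statistical methods to explore factors that moderate outcomes, including attrition rates and, if appropriate, levels of presenting severity". It does not say how attrition would be modelled, how a result would be interpreted, or whether attrition means leaving the groups or missing assessments.

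Four other places bear on it.

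- **Design** asks "whether benefits from or engagement with either module can be predicted by week 1 measures", and whether drop-out is more frequent in the second module period than in the first. There, engagement and drop-out are things to be explained.
- **Sample size/Power calculation** expects 90–100 of the 120 randomised to be retained at week 8. It then predicts that "this initial recruitment level would provide follow-up assessments on about" 72–80 people at week 19 and 66–70 at 12 months. It adds that vocational status should be known for more people, since it does not depend on attending assessments.
- **Statistical analysis plan** defines the primary analysis as intention-to-treat: "everyone who was randomized will be included in the analysis regardless of participation (full or partial or none) in the intervention groups". On missing data it says "Mixed-model repeated measures analyses may be used for some analyses".
- **Ethical considerations** allows people who decline assessments to go on attending groups, so the two kinds of leaving are distinct.

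**The concern.** A moderator is a characteristic fixed before treatment, across whose levels the treatment effect differs. Presenting severity qualifies. Attrition does not: it happens after allocation, may depend on the module received and the response to it, and is accompanied by loss of many later self-rated and observer-rated scores. If people who are not improving tend to leave, those who remain will look better even when remaining does nothing for them.

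The predicted losses are large enough for this to matter. The trial is also meant to inform later studies, so a report that attrition moderates benefit could credit completion with an effect it does not have and misdirect retention strategy.

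**Working it through.** **1. Which reading does the sentence support?**

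- *Both items are moderators.* This is the natural reading, and it is the problematic one.
- *Both items are outcomes.* This fails, because presenting severity is a baseline characteristic.
- *Attrition is one of the outcomes, and severity belongs to a separate exploration of which severity levels go with improvement.* This is grammatically possible and agrees with the Design section.

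The text does not settle between the first and third.

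**2. Size of the group affected (figures from Sample size/Power calculation).**

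| Time | Expected number of 120 | Lost |
|---|---|---|
| Week 8 | 90–100 | 17–25% |
| Week 19 | 72–80 | 33–40% |
| 12 months | 66–70 | 42–45% |

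Of those seen at week 8, 72/90 = 80/100 = 80% are expected at week 19, so p = 20% leave in between. People lost before week 8 have no week-8 score and cannot enter a comparison of week 1–8 change.

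**3. Assumptions.** The article gives no SD of change, so its power statement ("0.05 with > 80 % power" for a change above 5 points) cannot be reproduced. I assume SD = 12, with a range of 10–14. For scale, 12.0 is the largest SD at which a single arm of 45 has 80% power for a 5-point pre-post change at two-sided 0.05: 5 × √45 / (1.96 + 0.84) ≈ 12.0. I also assume 95 people at week 8 (19 later leavers, 76 stayers), no effect of staying, and a correlation r between poor week-8 change and a latent tendency to leave. No value of r is in the document.

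**4. Spurious stayer-leaver gap.**

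Gap = r × SD × φ(z) × [1/(1−p) + 1/p], with p = 0.2, z = 0.842, φ(z) = 0.280.

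Factor = 0.280 × (1.25 + 5) = 1.75. Standard error = 12 × √(1/19 + 1/76) = 3.08.

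| r (latent) | Gap, SD 12 | Significant at two-sided 0.05 |
|---|---|---|
| 0 | 0 | 5% |
| 0.1 | 2.1 | about 10% |
| 0.2 | 4.2 | about 28% |
| 0.3 | 6.3 | about 53% |

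At r = 0.3 the gap is 5.2 to 7.3 points for SD 10 to 14, above the plan's 5-point benchmark. If r were instead the ordinary correlation with observed leaving, the gap would be r × SD / √[p(1−p)] = r × 12 / 0.4, giving 3, 6 and 9 points.

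**5. Check with a different drop-out model.** In a simulation of 120 people (4,000 trials per setting, no effect of staying, no module difference), the log-odds of drop-out fell by 0, 0.3, 0.5 or 0.8 per SD of better change. The completer-dropout gap was 0, about 0.30, 0.47–0.48 and 0.71–0.73 SD. For the three non-zero settings it was significant in 25%, 56% and 90% of trials at 20% drop-out, and in 35%, 74% and 97% at 40%. This treats change as known for everyone, so it tests the mechanism rather than an analysis the trial could run exactly.

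**6. Module contrast.** In the same simulation the module-by-attrition interaction was significant in about 5% of trials in every setting, because drop-out worked identically in both arms. If leaving depended on response in one module only, the contrast among stayers would shift by r × SD × φ(z)/(1−p) = 0.42, 0.84 and 1.26 points for r = 0.1, 0.2 and 0.3. That is less than half the standard error of that contrast, 12 × √(2/38) = 2.75.

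**The case against.** The strongest reply is that this is half a clause under additional analyses in a self-described exploratory feasibility trial. The Background lists engagement among the secondary outcomes, the Design section treats engagement and drop-out as things to predict, and Table 1 schedules sessions attended as an assessment. Much of the remedy is therefore already in the article's thinking. That stands, and it limits the severity. It does not remove the point, because the analysis sentence does not carry the sounder framing over.

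A reader might infer that the analysis is bound to produce a false link. The documents do not support that: the gap is zero when leaving is unrelated to response, and no drop-out mechanism is described. Nor is a stayer-leaver difference false in itself. If poor responders leave, the association is real, and it misleads only if read as an effect of staying, which the article nowhere says it will do.

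A reader might also infer that the comparison of modules is compromised. That needs drop-out to depend on response differently by module, and even then the illustrative shift is small. The next steps listed in the Discussion do not include choosing between modules.

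Finally, it would be wrong to say that leavers have no later outcome at all. Vocational status is expected for a larger sample, and leaving the groups is not the same as missing assessments.

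**Conclusion.** The point holds in limited form. Read naturally, the plan names a post-randomisation event as a moderator, and an exploratory comparison of stayers with leavers is then liable to show an apparent benefit of staying when there is none. About 2 to 6 points is an illustration only: it rests on an assumed SD of 12, 20% later leaving and a latent correlation of 0.1 to 0.3, none of which except the 20% comes from the article.

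A reader might go further and suspect the primary result. That does not follow, since the intention-to-treat analysis does not condition on attrition. Severity is minor to moderate and confined to exploratory work.

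**What to change.** In the Statistical analysis plan section:

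- Take attrition rates out of the moderators and limit moderators to values recorded at enrolment or week 1.
- Analyse attrition as an outcome: retention at weeks 8 and 19 by randomised sequence and by week-1 variables, in all 120, with leaving the groups and missing assessments defined and reported separately.
- Use earlier change by later drop-out status only to examine the missing-data assumption behind the mixed model.
- Label any association between attendance and benefit as non-causal.

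If attrition was always meant as an outcome, the same edit simply brings this section into line with Design. The cost is a few lines of wording and no new data. All that is given up is an exploratory result that could not have been read as moderation.

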### Ethical considerations

The Human Ethics Research (HREC) Committee of the University of Sydney Australia has approved this study (2012/1639).

The group interventions are designed as an adjunct, not an alternative to usual treatments offered by the youth mental health services. As such, all participants are encouraged to continue to follow the healthcare advice of their treating clinicians and to remain in their care, as well as attending the groups. This usual treatment may include medication, counseling and/or referrals to a range of specialist mental health treatments or services.

Individuals who decline to complete follow-up questionnaires or assessments will be allowed to complete any groups they wish to attend. Also, in the follow-up phase (which includes the third school term), individuals may be allowed re-entry into groups if this is deemed clinically appropriate. For these cases, the data on weeks 1–19 will be included in the ITT analysis, but they will be excluded from some per-protocol analyses.

## Discussion

This trial examines the YES program which comprises two group modules that address mental health, developmental and physical health issues that are common features of the clinical presentations seen in young people attending youth mental health services. The modules use a youth-friendly format to try to maximize engagement by men and women. If the findings of this exploratory trial demonstrate benefits in the target domains, then it will be important to extend the research (a) to compare the YES to a control intervention in an RCT; (b) to undertake an explanatory study of putative mediators of change; and (c) to conduct a multi-center trial with a number of trained therapists offering the group modules and to examine outcomes over a longer follow-up period.

### Trial status

Recruitment is underway, and a poster describing the study was presented at the meeting of the International Society of Affective Disorders, Berlin, April 2014.

## Abbreviations

ADHD: attention deficit hyperactivity disorder
ASSIST: Alcohol, Smoking & Substance Involvement Screening Test
BDQ: Brief Disability Questionnaire
BMI: Body Mass Index
BMRI: Brain & Mind Research Institute
CBT: Cognitive Behavioural Therapy
DSM-IV: *Diagnostic and Statistical Manual of Mental Disorders, version IV*
EIP: early intervention in psychosis
FAST: Functional Assessment Short Tool
FBC: Full Blood Count
HREC: Human Research Ethics Committee
IPAQ: International Physical Activity Questionnaire
ITT: Intention to Treat
IPT: Interpersonal Therapy
K-10: Kessler Psychological Distress Scale
LFTs: Liver Function Test
PSQI: Pittsburgh Sleep Quality Index
RCT: Randomized Clinical Trial
RSEQ: Rosenberg Self Esteem Questionnaire
SD: Standard Deviation
SOFAS: Social and Occupational Functioning Assessment Scale
SPHERE 12: Somatic and Psychological Health Report
WHOQOL: World Health Organization Quality of Life Scale
YES: Youth Early-intervention Study (program)
